### Safety assessment

2.10

The data for safety assessment of the trial product will be based on the safety group. The safety population (SP) group is composed of all participants who will undergo at least 1 intervention and post-intervention safety assessment.

Adverse events: either the Chi-square or Fisher exact test will be performed to compare the differences between groups, and a summary sheet for each body organ will be created. In addition, the incidence rate of adverse events that are confirmed to be associated with either the trial product or the placebo product will be comparatively assessed using the same method.Laboratory test values: after completion of the trial, the fraction of incidences that exhibit clinical test values exceeding the normal range will be assessed using either Chi-square or Fisher exact test.Vital signs: means and standard deviations for blood pressure and heart rate will be recorded at each visit. Furthermore, significant changes in the categories of vital signs between the start and the end of the intervention will be assessed using either paired *t* tests or Wilcoxon signed rank tests.

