### Study aims and hypothesis

1.2

The primary aim of this study is to evaluate the efficacy and safety of SSHT versus placebo for the treatment of AD patients with gastrointestinal disorders in randomized clinical trials. We hypothesize that SSHT is more effective than placebo for the treatment of AD patients with gastrointestinal symptoms. To assess the efficacy and safety of SSHT, a randomized, double-blinded, and placebo-controlled trial will be conducted.

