#### Exclusion criteria

2.2.3

1.Patients receiving treatment for severe AD (antihistamines, adrenocortical hormones, Korean traditional herbal medication)2.Patients who have previously used oral antihistamines, steroids, antibiotics, systemic photochemotherapy, and other immune suppressants in the previous 4 weeks3.Patients with systemic infections or under treatment with systemic antibiotics4.Patients with severe dermatological disorders aside from AD, pigmentation, or large scarring of the area affected by AD5.Patients currently receiving interferon (IFN) drug treatments (IFN-α, IFN-β)6.Patients with liver diseases (liver cirrhosis, liver cancer)7.Patients with platelet count ≤100,000/mm^3^ due to chronic hepatitis-induced liver dysfunction8.Patients with kidney diseases (acute/chronic renal failure, renal syndrome)9.Patients with acute severe cardiovascular diseases (cardiac failure, myocardial infarction, cerebral infarction)10.Patients with a history of antipsychotic drug use within 2 months before the screening examination11.Patients who have participated in other clinical trials within the past 4 weeks12.Patients with a history of hypersensitivity or allergic reaction to an ingredient of the clinical trial product or the product itself13.Patients with a history of drug or alcohol abuse14.Patients who are pregnant or breastfeeding15.Patients who may become pregnant and have not used appropriate contraceptives (excluding those who have undergone sterilization surgery)16.Patients who are judged ineligible to participate in the trial by the principal investigator for other reasons, including diagnostic radiology outcomes

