### Sample size calculation

2.7

As the primary outcome to evaluate the efficacy of SSHT in patients with AD experiencing gastrointestinal disorders, this study will use the SCORAD scores. We calculated the sample size based on the previous study which evaluated the efficacy of Shiho Cheong gan-san for patients with AD.^[23]^ It is hypothesized that the mean changes of the SCORAD score in the SSHT and placebo groups after 4 weeks of intervention were 13.8 (μt) and 7.9 (μ*c)*, respectively and the standard deviations of the SCORAD scores between 2 groups were 8.2. A total of 60 participants, 30 in each group, are needed to achieve a statistical power of 80%, significance level of 0.05 in 2-tailed test, based on an estimated 20% dropout rate.

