### Safety and adverse events

2.13

In this clinical trial, the participants will undergo blood and urine tests during the initial screening visit (before consumption of the trial product) and at week 4 (4 weeks after initial consumption of the trial product) for safety assessment. In order to investigate the adverse events, the participants will be asked to return for an in-person interview at week 8 (1 month after the end of the trial product consumption) as a follow-up assessment of adverse events. In the case of adverse events, the principal investigator will record all relevant information (including the dates for the start and end of the adverse event, the severity, association with the trial product and associated interventions, treatment, and outcome) on the CRF. In addition, all clinically significant abnormal findings in laboratory tests or vital sign assessments will be recorded as adverse events.

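### Section 2.10 fixes only an out-of-range comparison for laboratory values; a baseline-adjusted comparison of the measured values should be added, because a general moderate shift would often go undetected

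*Protocol article*

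**What the plan says.** Section 2.10 (Safety assessment) sets the laboratory method in one sentence: "the fraction of incidences that exhibit clinical test values exceeding the normal range will be assessed using either Chi-square or Fisher exact test". It does not say that groups are compared, but these tests on fractions imply it, and the adverse-event item just before uses the same tests for group differences. No mean, change from screening, shift table or adjusted comparison is named for laboratory values.

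Section 2.13 (Safety and adverse events) gives the sampling: "the participants will undergo blood and urine tests during the initial screening visit (before consumption of the trial product) and at week 4". It adds that "all clinically significant abnormal findings in laboratory tests or vital sign assessments will be recorded as adverse events".

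Other continuous data are handled on their own scale. For vital signs, section 2.10 says "means and standard deviations for blood pressure and heart rate will be recorded at each visit", followed by paired tests from start to end of the intervention. Section 2.9 (Efficacy assessment) uses a baseline-adjusted analysis of covariance between groups. Section 2.8 contains only a general statement that methods will suit the type of measurement and its distribution.

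Safety belongs to the main objective in section 1.2: "The primary aim of this study is to evaluate the efficacy and safety of SSHT versus placebo".

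**The concern.** A count of values beyond the normal limit treats all movement inside the range as no change. Liver and kidney disease are exclusion criteria (section 2.2.3), so few values are likely to be out of range at entry, and with 24 to 30 children per arm a test on such small fractions has little power. If SSHT shifted a liver or renal marker by a moderate amount across most children, the expected result of the named test would be non-significant, while the numbers that could show the shift had been collected. The report could then state that no laboratory difference was found, on the strength of a test unlikely to find one of that kind.

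**Working it through.** **The plan's own figures.** The article gives no effect, rate or power for laboratory values. The only usable inputs are the design figures in section 2.7: 30 children per arm, 80% power, a two-tailed 0.05 level and an allowance of 20% for dropout. Evaluable numbers are therefore taken as 30 × 0.8 = 24 per arm, with 30 per arm as the upper case. (The standard formula does not return 60 from section 2.7: 2 × (1.960 + 0.842)² × (8.2/5.9)² = 30.3, so 31 per arm, and 31/0.8 = 38.75, so 39 per arm or 78 in all. That is a separate matter and the present point does not depend on it.)

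**Assumptions, because the plan has none.** Values are normal. SSHT shifts the mean by d standard deviations towards the limit, equally in all children. A share p0 of placebo values (2.5%, 5% or 10%) lies beyond the limit. Tests are two-sided at 0.05. Two shifts are shown: d = 0.5, and d = 5.9/8.2 = 0.72. The second is the plan's standardised SCORAD effect, used only as a yardstick; it says nothing about any laboratory marker.

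**Formulas.**
- SSHT out-of-range share: p1 = 1 − Φ(z(1−p0) − d). With p0 = 5%: 1 − Φ(1.645 − 0.5) = 12.6%, and 1 − Φ(1.645 − 0.72) = 17.8%.
- Fisher and uncorrected Chi-square power: exact, by summing the two binomial distributions over all tables with p ≤ 0.05.
- t-test power: noncentral t with 2n − 2 degrees of freedom and noncentrality d√(n/2). At n = 24: 0.5 × √12 = 1.73, and 0.72 × √12 = 2.49.

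**Results (power, %).**

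| n per arm | p0 | d | Fisher | Chi-square | t-test |
|---|---|---|---|---|---|
| 24 | 2.5% | 0.5 | 2 | 5 | 40 |
| 24 | 2.5% | 0.72 | 6 | 15 | 69 |
| 24 | 5% | 0.5 | 6 | 14 | 40 |
| 24 | 5% | 0.72 | 17 | 29 | 69 |
| 24 | 10% | 0.5 | 13 | 21 | 40 |
| 24 | 10% | 0.72 | 28 | 39 | 69 |
| 30 | 5% | 0.5 | 5 | 18 | 48 |
| 30 | 5% | 0.72 | 17 | 37 | 78 |
| 30 | 10% | 0.5 | 13 | 24 | 48 |
| 30 | 10% | 0.72 | 33 | 46 | 78 |

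At p0 = 5%, d = 0.72 and 24 per arm, the smaller expected count is 24 × (0.05 + 0.178)/2 = 2.7. By the usual rule (expected counts below 5) Fisher would be chosen, so its column is the closer guide there.

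**With the screening value as covariate.** For an assumed correlation of 0.6, d becomes d/√(1 − 0.36) = d/0.8, that is 0.625 and 0.90. Power at 24 per arm is then about 56% and 86%.

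**A second view.** Take the shift that the t-test finds with 80% power: 0.83 SD at 24 per arm, 0.74 SD at 30. After the cut, power is 6% to 39% with p0 of 2.5% to 5%, and 35% to 50% with p0 of 10%.

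**Where the loss shrinks.**
- At d = 1.5, the cut analysis has at least 78% power over the same range of p0 and n. The t-test is close to 100%, so the worst case is still about 22 points (Fisher, 24 per arm, p0 = 2.5%); with p0 of 5% to 10% the gap to Fisher is about 11 points or less.
- If 20% of placebo values are out of range, the 80% shift is found with 47% to 59% power.
- If only some children react (simulation, 3,000 runs, 24 per arm, p0 = 5%, correlation 0.6, mechanism assumed):

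| Reacting share and rise | Fisher | Chi-square | t-test | ANCOVA |
|---|---|---|---|---|
| 15%, 3 SD | 18 | 30 | 21 | 26 |
| 20%, 3 SD | 31 | 45 | 33 | 39 |
| 25%, 4 SD | 53 | 66 | 57 | 63 |

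Here Fisher is within a few points of the t-test, and Chi-square is about level with or ahead of ANCOVA.

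**The case against.** The strongest reply is that counting values outside the normal range is a usual safety summary with a clinical reason behind it: movement within the range is not in itself harm. That stands, and the comparison should stay.

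A second reply is that this is a condensed article, that means and shift tables are often left to an analysis plan, and that section 2.8 promises suitable methods. An unseen plan may indeed contain more. But section 2.10 does not leave the laboratory method open. It names one, and the general sentence in section 2.8 adds nothing specific to it.

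A third is that section 2.13 turns clinically significant laboratory abnormalities into adverse events, which are compared between groups. This protects individual children, but it too works by threshold and does not recover a shift within the range.

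A fourth concerns size: every laboratory input is assumed, and an equal shift in all children on a normal scale favours the t-test by construction. This stands and limits the claim, as the last table shows.

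Three stronger readings are tempting. One is that the planned test would miss laboratory effects in general; the results at 1.5 SD and for a reacting minority contradict that. Another is that the plan will treat a non-significant result as proof of laboratory safety; no sentence says so. The third is that vital signs receive the continuous between-group comparison denied to laboratory values. Section 2.10 names only start-to-end paired tests for them, so the contrast is one of measurement scale only. Nor can the number of numeric parameters be stated: no list is given, and some urine results may be categorical.

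**Conclusion.** The point holds in a limited form. The one laboratory analysis that section 2.10 names is valid for its own question but weak against a general moderate shift of about 0.5 to 0.8 SD. In the table above it gives up roughly 27 to 63 percentage points of power when Fisher is used, and 19 to 54 when Chi-square is used, against a t-test on the same values. These figures rest on normal values, a uniform shift, 2.5% to 10% of placebo values out of range and 24 to 30 children per arm, none of which the plan states for laboratory data. For a strong reaction in a minority the out-of-range comparison does about as well as the full-scale analysis. The two therefore complement each other, and naming only one leaves a foreseeable gap in a trial whose primary aim includes safety.

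**What to change.** In section 2.10, keep the out-of-range comparison and add, for each numeric blood parameter, a between-group ANCOVA of the week-4 value with the screening value as covariate, on the log scale where the distribution is skewed. Report the adjusted difference, or ratio on the log scale, with its 95% confidence interval. State that these are supportive estimates and not confirmatory tests, and that the laboratory safety conclusion will not rest on a non-significant Chi-square or Fisher p-value alone.

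The cost is a few lines of text and a few extra model runs on data already collected, with no added visits, samples or patients. The downside is multiplicity: with several parameters, some intervals will exclude no difference by chance. A mean shift also does not replace the out-of-range table for identifying individual children.

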### Study phase

2.3

When patients visit the trial center for the screening process, they will undergo different assessments, including blood and urine tests, and answer a survey questionnaire on AD symptoms by which the investigator may determine the patient's eligibility to participate in this clinical trial. At the screening visit, Lacticare (hydrocortisone-acetate 1% (100 g)) will be provided as a control variable which is the conventional therapy of AD to all participants. The amount and frequency of ointment usage from the screening visit to visit 3 (8-week time point) will be recorded. Patients found eligible to participate will be informed of their eligibility via a telephone call, and selected participants will be asked to visit the trial center (visit 1) within 2 weeks of the screening examination for random assignment into either the experimental group or the control group. After the assignment, the participant will undergo additional assessments (answering survey questionnaires including those on AD, as well as a physical examination) and will receive enough of the trial product for 4 weeks (to be used 3 times per day). After 4 weeks, participants will be asked to return for visit 2 to perform identical assessments (survey questionnaires and blood tests). For the following 4-week period, the participants will be asked to stop the usage of all medication, with the exception of Lacticare, and return for visit 3 after 4 weeks to undergo the same assessment. Detailed assessment types and the schedule used are outlined in Table 1.

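### The laboratory safety comparison takes no account of screening values, so out-of-range results present before dosing count the same as new ones and dilute any signal

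*Protocol article*

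**What the plan says.** Section 2.10 of the protocol article fixes both the measure and the test for laboratory values: "the fraction of incidences that exhibit clinical test values exceeding the normal range will be assessed using either Chi-square or Fisher exact test". The sentence opens with "Laboratory test values: after completion of the trial" and does not mention the screening result. I read the measure as covering values outside the range in either direction.

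For vital signs, the same section does use a starting value. It assesses "significant changes in the categories of vital signs between the start and the end of the intervention".

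Two sections describe when samples are taken:

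- Section 2.13 (Safety and adverse events): "the participants will undergo blood and urine tests during the initial screening visit (before consumption of the trial product) and at week 4". For the follow-up visit it says only that "the participants will be asked to return for an in-person interview at week 8", to ask about adverse events.
- Section 2.3 (Study phase): at visit 2 participants "perform identical assessments (survey questionnaires and blood tests"), and they then "return for visit 3 after 4 weeks to undergo the same assessment". Visit 3 is the week-8 visit, four weeks after the product is stopped.

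Section 2.13 also has laboratory abnormalities judged clinically significant logged as adverse events, and 2.10 compares adverse events between the arms.

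**The concern.** A between-arm comparison of laboratory abnormalities should show whether the product causes them. The measure as written mixes two kinds of participant: those out of range before dosing, who say nothing about the product, and those who became abnormal on it. The first group adds the same expected background to both arms, and the second has to be detected against that background.

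Such background is possible here. The exclusion criteria (2.2.3) name liver and kidney diseases and one form of low platelet count, but they do not require laboratory values to be within the normal range.

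Safety is part of the primary aim (1.2), the participants are aged 3 to 18, and each arm has only 30 participants, or 24 after the assumed 20% dropout. A comparison this small has little sensitivity to spare. The screening results needed to separate the two groups are already collected.

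There is also an unsettled point of timing: 2.3 and 2.13, read literally, disagree on whether blood is drawn at week 8.

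**Working it through.** **Inputs from the document.** 30 per arm, and 30 × 0.8 = 24 per arm after 20% dropout (2.7); two-sided 0.05; Fisher exact test (2.10). The article gives no design figure for the laboratory comparison, so there is none to reproduce. The total of 60 was set for SCORAD.

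**Inputs assumed.** The documents give neither the share b out of range at screening nor any rate of new abnormality. I take b from 0% to 40%, equal in both arms and persisting to week 4. For new abnormality among those in range at screening I take 30% or 20% on SSHT (p_T) and 2% on placebo (p_C).

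**Step 1: effect on the difference.** Under the rule as written, the expected proportion in an arm is b + (1-b)p. The between-arm difference is therefore

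[b + (1-b)p_T] - [b + (1-b)p_C] = (1-b)(p_T - p_C).

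With p_T - p_C = 30% - 2% = 28 points:

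- b = 0: 28 points
- b = 20%: 0.8 × 28 = 22.4 points (44.0% versus 21.6%)
- b = 40%: 0.6 × 28 = 16.8 points (58.0% versus 41.2%)

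**Step 2: effect on power.** Exact power of the two-sided Fisher test, by enumerating two binomials. The last column fixes the number in range at its expected value, N(1-b) rounded.

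| N per arm | b | New, SSHT vs placebo | Any out-of-range value | New, over all participants | New, among those in range at screening |
|---|---|---|---|---|---|
| 30 | 0% | 30% vs 2% | 0.81 | 0.81 | 0.81 |
| 30 | 20% | 30% vs 2% | 0.36 | 0.62 | 0.75 |
| 30 | 40% | 30% vs 2% | 0.18 | 0.36 | 0.54 |
| 30 | 20% | 20% vs 2% | 0.16 | 0.24 | 0.39 |
| 24 | 20% | 30% vs 2% | 0.28 | 0.58 | 0.58 |
| 24 | 20% | 20% vs 2% | 0.13 | 0.25 | 0.24 |

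Counting new abnormalities over all participants gives the same 22.4-point difference at b = 20% as the rule as written. Its gain comes from removing the background, which lowers the variance. Restricting to those in range also restores the 28-point difference, but on fewer participants. The two baseline-referenced columns differ irregularly because the Fisher test is discrete in samples of this size.

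**Step 3: single-table illustration.** Suppose 5 per arm are out of range at screening and stay so, with 5 new abnormalities on SSHT and none on placebo:

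- 24 per arm: as written 10/24 vs 5/24, p = 0.21; new only 5/19 vs 0/19, p = 0.046.
- 24 per arm with 4 new cases instead of 5: 9/24 vs 5/24, p = 0.34; 4/19 vs 0/19, p = 0.105.
- 30 per arm with 5 new cases: 10/30 vs 5/30, p = 0.23; 5/25 vs 0/25, p = 0.0502.

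The direction is the same each time, but whether the second test crosses 0.05 turns on a single event or on the arm size.

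**Step 4: the week-8 passages.** Section 2.13 names two sampling times, screening and week 4. Section 2.3 names blood tests at visit 2 and calls visit 3 the same assessment. Taken literally, these cannot both be complete. Week-4 samples exist under either section.

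**The case against.** The strongest defence is that 2.10 is silent on baseline and does not exclude it. The phrase about incidences could be read as new occurrences, and shift tables are often left to an analysis plan, which is not shown. Part of this stands: a later document may already handle it. But the article does more than stay silent. It names a measure and a test, and as worded that measure does not separate new from pre-existing values, although the vital-signs sentence beside it does refer to the start of the intervention.

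A reader might infer that new abnormalities on SSHT would be masked, or swamped by old ones. The documents do not support that. Randomisation balances screening abnormalities in expectation, the difference shrinks only by (1-b), and b is unknown. Chance imbalance at screening could equally create a false signal. Abnormalities judged clinically significant also reach the between-arm adverse-event comparison, a real second route, though it depends on the investigator's judgement.

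A reader might also infer that the laboratory test uses week-8 samples, taken off product. The opening phrase of the laboratory sentence more naturally says when the analysis is run, and 2.6 uses similar words for the timing of the statistical analysis. Table 1, to which 2.3 refers for the schedule, is not shown and may settle the sampling times. On-treatment week-4 data are not lost in either case.

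**Conclusion.** The point holds as a loss of sensitivity. The laboratory comparison is not referenced to screening, so pre-existing out-of-range values dilute the contrast in new ones by the factor (1-b). Under the assumed 30% versus 2% with 30 per arm, power at b = 20% is 0.36 as written, against 0.62 to 0.75 for baseline-referenced counts. At b = 0 the definitions coincide. These sizes rest on assumed rates, on equal b in the two arms and on persistence of the screening abnormalities. They show the direction and possible scale and do not predict this trial's results.

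The week-8 discrepancy between 2.3 and 2.13 is a secondary matter of wording to reconcile. It does not show that the wrong sample will be analysed. Because the better analysis needs no new data, the change is worth making although the size of the loss is unknown.

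**What to change.** Replace the laboratory sentence in 2.10, or specify in the analysis plan, as follows:

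- For each analyte, among participants in range at screening, compare by arm the proportion out of range at week 4 (Fisher exact test, difference with 95% confidence interval).
- Add a screening-to-week-4 shift table per analyte and arm, covering all participants with both samples, so that worsening in those already out of range is also visible.
- Reconcile 2.3 and 2.13 on whether blood is drawn at week 8. If it is, report those values separately as off-product values.

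The cost is wording only, since the screening and week-4 tests are already planned. The downside is a somewhat smaller denominator for the first comparison. Power stays low whichever definition is used, so the estimates and intervals should carry more weight than the p-values.
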